### Developing the education and assessment package

Within our trial, accredited pharmacists are appropriately poised to deliver education to patients at the HMR interview and to GPs through the HMR reports. Addressing both the patient and their GP in this fashion has been recognized as an important factor to increase the chance of improving patient outcomes through chronic disease management interventions [28,33,34]. Further education and specialization of accredited pharmacists in the area of ACS secondary prevention should increase the chance of the current service utilizing these opportunities for follow-on education.

The accredited pharmacist education and assessment package will consist of five online lectures, as well as several separate resource documents for pharmacists to refer to at any point throughout the HMR service. The five online lecture topics are: an introduction to the trial and the evidence to practice gaps for ACS; background information about the hospital management of ACS; the importance of cardiac rehabilitation and lifestyle modifications; evidence-based ACS medication management; and methods for improving adherence to therapy following ACS. The separate resource documents include a 'chest pain action plan', information on the use of short-acting nitrates, and links and referral to specific material available from the National Heart Foundation, Australia. The material will be assessed using case-based examples with multiple-choice questions (pass mark of 75%). The full details of the development of the education and assessment package will be published at a later stage.

### Outcomes

All outcomes will be measured using blinded assessment processes at the two study endpoints of six and twelve months post-discharge. Each outcome will be a comparison between the control and intervention groups. A proposed conceptual framework for the standardized evaluation of chronic disease management interventions has been considered in the selection of the trial outcomes and further trial evaluation [28]. Using a framework to guide outcome selection has not only helped to ensure that we are measuring the important clinical outcomes from the intervention, but also highlighted the individual steps of the intervention that require monitoring. Monitoring these individual steps, such as pharmacist detection of drug-related problems and GP acceptance of pharmacist recommendations, is important to measure the level of alignment between the theoretical plan and the practical application of the intervention. Such detailed monitoring and outcome reporting may also elucidate areas of practice worthy of further focus in future research.

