The Home Medicines Review (HMR) program is an existing community-based service that has the potential to be tailored to meet the needs of patients recently discharged from hospital following ACS. Although this potential has not been fully realized in the past [15], HMRs may be used to particularly target patients' persistence and adherence to guideline-based medications following ACS. The HMR service currently involves general practitioner (GP) referral of patients to an HMR-accredited pharmacist, often through a community pharmacist liaison [16]. The accredited pharmacist will visit the patient in their home, discuss their medication taking habits, and provide education or adherence interventions where required. Following the home visit the accredited pharmacist writes a report for the GP noting their observations and any clinical adjustments that could be made to the patient's medication regimen. Based on this report, the GP is expected to complete an agreed management plan, selecting the accredited pharmacist's recommendations which they agree to implement and/or follow up. The service is currently available in Australia, free of charge to Australian citizens under funding arrangements through the public health system, Medicare Australia. The GP, accredited pharmacist, and community pharmacist involved with an HMR service are paid by way of reimbursement from Medicare Australia. One of the eligibility criteria for HMRs is recent hospital discharge [16] and the HMR service has been demonstrated to be feasible as a post-discharge service for patients following ACS in the Australian healthcare setting [17]. However, the effect of this service on clinical outcomes following ACS is unknown.

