### Controls

Following randomization to the control group, patients will be offered the usual care processes involved with post-discharge management of ACS in Australia. Through the public health system, patients are able to attend a cardiac rehabilitation program at their local hospital as well as a cardiologist follow-up appointment, usually occurring at one month following discharge. The cardiac rehabilitation programs from the two different hospitals may vary slightly in their level of physical activity, but the material covered in their information sessions is similar.

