### Intervention

Patients in the intervention group will receive a dHMR at approximately two months following discharge as well as usual care. The time of two months post-discharge was selected as previous studies of ACS patients have demonstrated that the period between one and three months post discharge is when patients are most vulnerable for medication discontinuation [2,3,32]. This suggests that a service addressing both the educational and clinical management aspects of therapy may be most beneficial when offered in this time period.

Based on the existing funding arrangements and recommended reasons for referral, the HMR service is currently available in Australia for all ACS patients following hospital discharge [16]. The uptake of this service, however, may be largely limited by the absence of HMR referral systems in this transitional period. Furthermore, the currently available service could be tailored to maximize the potential for benefit from this service in the ACS population. We propose to add to the existing HMR service in several ways, making the proposed dHMR service more directed toward the ACS population.

Typically, HMRs are ordered by a referral letter generated by the patient's GP. Referral letters may vary significantly in their level of detail, potentially leaving the pharmacist with little direction prior to the patient interview. This concern was highlighted as a potential downfall of the service in a qualitative review that was conducted in 2008 [15]. To address this issue, the enrolling researchers will use a specifically designed database that allows baseline data collection to automatically populate sections of the HMR referral. The referral letter will still be sent to the GP for approval and addition of any further information, such as medications that have changed since discharge. GP approval is a requirement for payment under the existing public service arrangements, and having the GP engaged with the intervention early should increase their willingness to participate. This new approach, however, relieves the GP from having to complete most of the referral data and allows for simple addition of only useful information. The GP may also find the information on this referral letter useful when they receive the letter, as previous research has demonstrated that standard discharge letters following ACS admissions do not always contain a sufficient level of information and sometimes take too long to reach the GP [3].

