### Secondary outcomes

Secondary outcomes will include hospital readmission rates, length of hospital stays, changes in quality of life, cardiac rehabilitation completion rates, smoking cessations rates, and mortality. Hospital readmissions and mortality will be further categorized as ACS-related or due to other causes. Quality of life will be measured at six weeks post-discharge as a baseline, pre-dHMR measure and again at both study endpoints. The Euroqol 'EQ-5D 3 L' [42] will be used to measure general quality of life and the Seattle Angina Questionnaire (SAQ) [43] will be used to measure cardiac-specific quality of life. Both instruments have been validated when administered individually [43-46] and in combination [47] to assess quality of life in patients with coronary heart disease. In addition to a self-report of smoking status at baseline and the study endpoints, we will be further categorizing each smoker's dependence on cigarette smoking using the Fagerstrom Test for Nicotine Dependence (FTND) [48].

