### Data collection

Baseline data collection will occur in hospital at the time of enrolment, immediately post-discharge from hospital and at six weeks post-discharge - when the participants will be sent their first questionnaire set. The in-hospital baseline data collection will include the recording of traditional coronary risk factors, as well as the 'cholesterol' version of the INTERHEART Modifiable Risk Score (IHMRS) [64]. This will allow for baseline comparison of risk between the two groups. Although not validated to calculate risk in a population of patients following a coronary event, the IHMRS requires the recording of risk factors in a way which emphasizes their correlation to their level of actual risk and this remains relevant, regardless of the patient's degree of heart disease. For example, the IHMRS requires the recording of smoking status into several cutoffs depending on the number of cigarettes smoked per day, which correlates independently to heart attack risk, as opposed to simply recording cigarette smoking status in an arbitrary fashion, which is of lesser value with regard to risk comparisons. The final baseline data collection point of six weeks post-discharge for questionnaire mail-out reflects our intention to gauge each patient's status on each of the questionnaires in the time directly before the HMR and not while in hospital, as factors, such as adherence behavior, may be very high in hospital but may significantly decline over time following discharge [2,3,14,65,66]. Patients in the intervention group will be asked to ensure that they complete their questionnaire before their pharmacist visit and pharmacists will record whether or not this has happened as reported by the patient. Patients in the control group will be given a reminder telephone call if their questionnaires have not been returned by three weeks from the mail-out date.

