Although based on an existing, Medicare-funded service, the treatment protocol faces several potential barriers to success. Largely, this includes interprofessional barriers, such as GP approval of the dHMR referrals and GP acceptance of pharmacists' recommendations. The former point will be aided by the enrolling researcher contacting the GP once randomization has been revealed. Although GP approval of dHMR referrals may affect the uptake of the intervention in this trial, the use of a consistent and informative referral letter and a telephone conversation to support this letter, could prove to be advantageous over the current systems for initiating standard HMR referrals, which may not always be this well-structured. The other barrier of GPs not accepting pharmacists' recommendations has been raised due to previous research showing that GPs only action approximately 45% of pharmacist's recommendations following HMRs [68,69]. The educational material provided to accredited pharmacists completing this trial, however, should help guide pharmacists to make recommendations which will be relevant post-ACS and simple to implement. Furthermore, as the education package has been based on the latest evidence in ACS management, even if GPs do not accept all of the pharmacists' recommendations, they should still be gaining useful information from the dHMR reports. This may lead to improved ACS management, irrespective of the rate at which GPs accept pharmacists' individual recommendations.

Having the pharmacists complete the online training package may also be another barrier to the successful implementation of the trial protocol. The education and assessment package should take approximately three hours to complete and will be rewarded with recognition of continuing professional development and an AUD$50 honorarium. We hope that these incentives and the easy-to-use format of the material will help facilitate the completion of the package. Through careful consideration of the potential barriers recognized above, the dHMR processes that we have developed have transformed these barriers into opportunities to improve the implementation of the intervention.

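### The protocol says every outcome is assessed blind, but quality of life, smoking and all other questionnaire outcomes, including the Morisky fallback for the primary outcome, are reported by patients who are not blinded

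*Protocol article*

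**What the plan says.** The Outcomes section makes a blanket statement: "All outcomes will be measured using blinded assessment processes at the two study endpoints of six and twelve months post-discharge".

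The rest of the article describes what patients see and how the outcomes are obtained.

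- **Intervention arm (Intervention section):** "Patients in the intervention group will receive a dHMR at approximately two months following discharge as well as usual care". The section on ACS post-discharge services says what such a review involves: "The accredited pharmacist will visit the patient in their home, discuss their medication taking habits, and provide education or adherence interventions where required".
- **Control arm (Controls section):** "Following randomization to the control group, patients will be offered the usual care processes involved with post-discharge management of ACS in Australia". No sham or attention visit is described.
- **Secondary outcomes:** quality of life is measured with the EQ-5D 3L and the Seattle Angina Questionnaire (SAQ). Smoking is covered by the words "In addition to a self-report of smoking status at baseline and the study endpoints", with the Fagerstrom Test for Nicotine Dependence (FTND) added for smokers.
- **Process outcomes:** further patient questionnaires cover illness perception, risk perception, beliefs about medicines, self-efficacy and adherence behaviour.
- **Data collection:** follow-up at six and twelve months consists of dispensing records from pharmacies, hospital register checks, a deaths registry check, and questionnaires sent by mail with a telephone reminder.
- **Primary outcome:** adherence is defined by MPR from dispensing records. If those records have a significant shortfall, self-report on the four-item Morisky questionnaire is used instead.

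**The concern.** For a questionnaire outcome, the person who makes the assessment is the patient. If the patient knows which treatment was given, the outcome is not blinded, whoever opens the envelope or adds up the score.

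This matters here because the intervention targets the behaviours that are then self-reported. The Background says that the patient interview takes a motivational approach, and the pharmacists' training package covers lifestyle change and ways of improving adherence. A patient who has had such a visit may answer questions on smoking, medicine-taking or well-being differently for that reason alone.

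A reader who relies on the Outcomes sentence would credit differences on these measures with a protection that they lack. The same would apply to the primary outcome if the Morisky fallback were used.

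**Working it through.** The point is one of consistency, so the main check is to set the statements side by side.

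**Step 1: do patients know whether they were visited?** The article does not say so in words, but the inference is secure. The intervention is a face-to-face visit at home, and the comparator is usual care without a substitute visit. Intervention patients are also told of the visit in advance: "Patients in the intervention group will be asked to ensure that they complete their questionnaire before their pharmacist visit". That instruction concerns the six-week baseline questionnaire. It therefore shows awareness of the visit before either endpoint, not how the endpoints are assessed. Nowhere does the article say that patients are blinded.

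**Step 2: who supplies each endpoint?**

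| Outcome | Source at 6 and 12 months | Can assessment be blinded? |
|---|---|---|
| MPR (primary) | Dispensing records | Yes |
| Morisky (primary, fallback) | Patient | No |
| Readmission, length of stay | Hospital register | Yes |
| Mortality | Deaths registry | Yes |
| ACS-related or other cause | Classification of the events above | Yes |
| EQ-5D, SAQ | Patient | No |
| Smoking status, FTND | Patient | No |
| Belief, perception, self-efficacy and behaviour scales | Patient | No |
| Cardiac rehabilitation completion | Source not named in the article | Depends on the source |

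**Step 3: compare with the statement.** The sentence covers all outcomes at both endpoints. The table has several rows for which that is impossible. One of them is a possible form of the primary outcome.

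**Step 4: is any figure in the plan affected?** No. The sample size reproduces. For 45% against 60%, two-sided alpha 0.05 and 80% power, the normal-approximation formula gives 173 per group, and 186 with the continuity correction. Then 2 × 186 = 372, and 372 / 0.8 = 465, as stated. Nothing in this point changes those numbers.

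**Step 5: what would determine the size?** Suppose the true adherent share p is the same in both arms, and that non-adherent patients report themselves adherent at rates r1 (intervention) and r0 (control). The spurious difference is then

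(p + (1 − p)·r1) − (p + (1 − p)·r0) = (1 − p)(r1 − r0).

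Only the excess r1 − r0 matters; equal misreporting cancels. With the protocol's planning value p = 0.45, the multiplier is 0.55. An assumed excess of 5, 10 or 15 percentage points would give 2.75, 5.5 or 8.25 points, against the 15-point target difference. The excess is purely an assumption, and 45% was not set for the Morisky scale. This is therefore a conversion rule and not an estimate for this trial.

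**The case against.** The best defence is that the sentence speaks of blinded processes and not of blinded patients. On that reading, staff who receive, score and enter the forms are unaware of allocation. That is feasible for mailed questionnaires. The article is also open that smoking and Morisky are self-reports, and the questionnaire outcomes are already secondary or process measures. All of this is fair, and it makes the matter one of an over-broad statement rather than a concealed defect. It does not rescue the word covering every outcome, because blind scoring leaves the answer itself unblinded.

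A reader might also draw three stronger conclusions, which the document does not support.

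- **That unblinded staff classify contraindications or the cause of readmissions and deaths.** The enrolling researcher does unlock the allocation (Randomization section), and the Discussion, on obtaining GP approval of referrals, adds: "The former point will be aided by the enrolling researcher contacting the GP once randomization has been revealed". But the article gives that person no role at six or twelve months. Classification is itself outcome assessment, which the Outcomes section says is blinded. Who does it, and from which extract, is detail that an article may leave to the full protocol.
- **That socially desirable answering arises in the visited arm only.** Under Setting, patients generally receive lifestyle education and medication counselling before discharge. Under Controls, patients are offered cardiac rehabilitation with information sessions. Misreporting is possible in both arms; the issue is an excess in one.
- **That a bias of a particular size is to be expected.** The article gives no misreporting rates, so none can be calculated.

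**Conclusion.** The blinding statement is wrong as written. It can hold for dispensing-based MPR, readmission, length of stay, mortality and the classification of these. It cannot hold for the EQ-5D, SAQ, smoking status, FTND and the other mailed questionnaires, nor for a primary outcome based on Morisky.

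The conclusion rests on one inference, that patients know whether they had the home visit. The absence of a sham visit and the advance notice given to intervention patients make that inference safe. The MPR-based primary outcome is untouched. The only documented route by which self-report reaches the primary outcome is the Morisky fallback. The size of any resulting bias is unknown.

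**What to change.** Replace the blanket sentence with one that separates the two kinds of outcome, for example: *Outcomes taken from dispensing records, hospital registers and the deaths registry, including their classification, will be assessed blind to allocation. Questionnaire outcomes are reported by patients who are not blinded.* Place cardiac rehabilitation completion on one side or the other according to its source.

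In addition:

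- Label quality of life, smoking, FTND and all other questionnaire results as unblinded patient self-report wherever they are presented, and interpret differences on them with that caveat.
- If the Morisky fallback is used, label that primary result in the same way, and keep the dispensing-based MPR result as the blinded primary evidence.

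The cost is a change of wording before recruitment, which according to the article has not yet begun. No instrument, visit or sample size changes. The small downside is a weaker stated claim for the questionnaire outcomes.

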### Primary outcome

The primary outcome will be the proportion of patients who are adherent to a complete, guideline-based ACS medication regimen at the trial endpoints. The accepted definition of adherence for this trial will be a medication possession ratio (MPR) of 80% to 120% for all guideline-based medications, which is a commonly accepted cut-off for this measure [35-39]. MPR will be determined by dividing the total number of days of medication supplied by the total specified time period. This value can be multiplied by 100 in order to be reported as a percentage of the time that the patient had medication available to take, a commonly used surrogate measure of adherence. During the baseline interview, we intend to record all possible pharmacies that a patient may attend in order to make the dispensing records complete. If, however, there is a significant shortfall in the completeness of dispensing records, we will use self-report of medication adherence as an alternate measure. The four-item Morisky adherence questionnaire will be used for this purpose [40]. This is a well-validated instrument, being used previously with good predictive validity in patients at risk of cardiovascular disease [40,41]. In the case where a patient has a clearly documented contraindication to one of the four guideline-based medication classes, their medication regimen may still be considered 'complete' provided they are taking all other guideline-based medications. For example, a patient with asthma not taking a beta-blocker but still taking aspirin, an ACE inhibitor, and a statin, will be considered in the same group as those prescribed all four medications. This primary outcome comprehensively assesses the overall impact of the intervention on both GP prescribing behaviors and patient medication-taking behaviors. In order to separately measure the recognized problem of persistence with guideline-based medications, we will complete a secondary analysis of the primary outcome in the group of patients who are prescribed a complete, guideline-based medication regimen at the time of discharge from hospital.

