### Objectives

In this study, we aim to investigate the effect of an adaptation of the currently available HMR service on guideline-based medication adherence and persistence following ACS. The service will be directed towards the needs of ACS patients by educating the accredited pharmacists involved about ACS-specific patient issues and through improving the continuum of care by providing consistent information in a structured HMR referral letter. As such, the trialed service will be termed a directed Home Medicines Review (dHMR). This is the first trial in a series of studies entitled 'Medication Reviews ReDirected (MedReDi)' which refers to the plan for future research in this area, following a similar theme of minor adjustments to the currently existing HMR service, so that patients with other specific illnesses can be targeted through new dHMR services. The overall intention will be to help patients become more familiar and competent with their medication management aspect of therapy - more simply, helping patients become 'MedReDi'.

For the purpose of this study, guideline-based ACS medication therapy refers to the four medication classes as supported by ACS guidelines [25-27]. These medication classes include: angiotensin-converting enzyme (ACE) inhibitors/angiotensin II receptor blockers (ARBs); antithrombotics (aspirin and/or clopidogrel/prasugrel and/or warfarin); beta-blockers; and statins.

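### The uncapped possession ratio with an 80-120% band misclassifies some adherent patients, whether it is summed by class or taken per drug over the full window

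*Protocol article*

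**What the plan says.** The Primary outcome section of the Protocol article sets adherence as "a medication possession ratio (MPR) of 80% to 120% for all guideline-based medications". It gives the formula: "MPR will be determined by dividing the total number of days of medication supplied by the total specified time period". It then says the result, as a percentage, can be "reported as a percentage of the time that the patient had medication available to take". The article does not cap the ratio or say whether it is formed per drug or per class. It also gives no rule for concurrent agents or for a change of agent.

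The Objectives section defines therapy at class level: "guideline-based ACS medication therapy refers to the four medication classes as supported by ACS guidelines". One of the four classes is "antithrombotics (aspirin and/or clopidogrel/prasugrel and/or warfarin", so more than one agent at a time is expected in that class.

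The section on ACS post-discharge services describes the pharmacist's report to the GP as "noting their observations and any clinical adjustments that could be made to the patient's medication regimen". The Intervention section places the directed review at about two months after discharge, before both the six- and twelve-month endpoints.

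**The concern.** A ratio with an upper limit works when one medicine is supplied for one purpose throughout the period. Here the unit of therapy is a class, agents within a class may overlap, and the trial's own service may lead to changes of agent. An uncapped sum of days then mixes three things: how well the patient was covered, how many agents were prescribed together, and whether an agent was replaced. Only the first is adherence.

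The formula also does not deliver its stated meaning. A share of time with medicine available cannot exceed 100%, so an upper limit of 120% has no sense on that scale.

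The affected quantity is the primary outcome. The same section says this outcome should reflect GP prescribing as well as patient behaviour, so a measure that penalises a changed regimen works against its purpose. If changes are more frequent after the directed review, the error need not be equal in the two arms.

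**Working it through.** **Inputs.** The band, the formula and the all-medications requirement come from Primary outcome. The class definition comes from Objectives, and the two-month timing from Intervention. The 45% control rate, 15-point difference, 80% power, alpha of 0.05, 186 per group and 465 in total come from Sample size. Assumptions: windows T of 182 and 365 days, and a switch at day 60.

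**The plan's own figure.** A two-sided comparison of 45% v 60% at alpha 0.05 and 80% power needs 173 per group without continuity correction and 186 with it. The plan's 186 is therefore reproduced. Then 2 x 186 / (1 - 0.20) = 465, also as stated. The sample size is not at issue here.

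**Reading A: days summed within a class.**
- Two agents, both fully supplied: (T + T)/T = 200%, above 120%, classed non-adherent.
- First agent fully supplied, second agent for d days: (T + d)/T exceeds 120% once d > 0.2T. That is 36.4 days at six months and 73 days at twelve.
- Two agents each supplied for 60% of days: 0.6 + 0.6 = 120%, classed adherent.

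**Reading B: each drug separately, full window as denominator.**
- Two agents, both fully supplied throughout: 100% each, so the patient passes.
- Switch within a class at day 60, continuous cover, six months: 60/182 = 33% and 122/182 = 67%. Both are below 80%.
- Same switch, twelve months: 60/365 = 16% and 305/365 = 84%. The first drug fails, so the all-medications rule fails.
- In general, with continuous cover and no overlap the two shares add to 100%. Two drugs cannot both reach 80%, which would need 160%. The switch date does not matter.

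| Patient | Summed by class | Per drug, full window |
|---|---|---|
| Two antithrombotics, both fully supplied | 200%, fails | 100% each, passes |
| Two antithrombotics, each at 60% | 120%, passes | 60% each, fails |
| Switched at day 60, continuous cover, no overlap | 100%, passes | 33%/67% (six months), 16%/84% (twelve), fails |

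**Effect on power (illustrative only).** Normal approximation for two proportions, 186 per group, two-sided 0.05, no continuity correction:
- No misclassification, 45% v 60%: 82.8%. This exceeds 80% because 186 includes the correction.
- 5% of adherent intervention patients lost, no controls: 0.60 x 0.95 = 57%; 45% v 57% gives 64.0%.
- 5% of adherent patients lost in both arms: 0.45 x 0.95 = 42.75%; 42.75% v 57% gives 78.7%.

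The 5% is an assumption. No loss rate appears in the document.

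**The case against.** The strongest reply is that the article names neither level of calculation. It applies the band to medications and explains the ratio as time with medicine available, and neither wording invites adding two agents to reach 200%. A third reading, days covered within a class, fits that explanation and misclassifies neither group. The specified period is also not expressly the full window for a drug no longer prescribed. A condensed article may leave such detail to an analysis plan that is not shown.

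Part of this stands. The missing level of calculation alone would not be a finding. But the uncapped sum and the 120% ceiling are stated, not omitted, and days covered is a different formula from the one printed.

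A reader might infer three stronger things, none of which the document supports:
- *Dual-antithrombotic patients are classed non-adherent outright.* This holds only if days are summed by class. Per drug, patients stably on both agents pass.
- *A switch breaches the 120% ceiling.* Per drug, the failure is on the 80% floor. Summed by class, a switch need not breach. With packs of P days refilled on time and a switch on day s, supply is P x (ceil(s/P) + ceil((T - s)/P)). Over 182 days, about 4% of switch days from day 60 exceed 120% with 30-day packs and about 51% with 28-day packs. Over 365 days none do (maximum 14 x 30/365 = 115%). Pack sizes are assumed.
- *The comparison is biased against the intervention by a known amount.* The Controls section gives control patients cardiologist follow-up, so their regimens can change too. The Discussion reports that GPs act on only about 45% of recommendations, and not every recommendation is a within-class switch. Class summing also errs the other way, by passing the 60%/60% patient.

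The band is also described as commonly accepted, with citations that cannot be checked here. That supports keeping it as a sensitivity analysis.

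**Conclusion.** The point holds in a limited form. Under either of the two readings worked through, the stated rule classes some well-covered patients as non-adherent. By class these are patients on two antithrombotics; per drug over the full window they are patients whose agent was switched. Class summing can also pass patients poorly supplied with both agents. The uncapped ratio does not match the meaning the article gives it.

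The 200% and 120% results follow from the formula alone. The 33%/67% and 16%/84% results rest on windows of 182 and 365 days and a switch at day 60, though the failure does not depend on the date. How many trial patients would be affected cannot be derived from the document. Bias against the intervention is plausible, since the review can prompt changes within the window, but its size and even its direction are not established. The fall in power from about 83% to 64% shows only what a 5% one-arm loss would do. This should be settled before the outcome is derived, because it concerns the primary endpoint.

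**What to change.** Replace the primary definition with a class-level measure of days covered. Suggested wording: *For each guideline-based class, adherence is the proportion of days in the follow-up window on which at least one agent of that class is in hand. Agents within a class are pooled, so a switch within the class does not interrupt cover. Early refills are carried forward, and the proportion is capped at 100%. A patient is adherent if the proportion is 80% or more in every class, subject to the existing contraindication rule.* Keep the 80-120% possession ratio as a sensitivity analysis, stating whether it is formed per drug or per class.

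The cost is wording and some programming. The dispensing records are already to be requested at six and twelve months (Data collection), and the Trial status section says recruitment has not begun. Two downsides should be stated. Results will be less directly comparable with studies using the 80-120% ratio, which the sensitivity analysis addresses. The class rule will also not detect a patient who stops one of two concurrent antithrombotics, so supply of each antithrombotic should be reported separately. The sample size needs no change.
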